### Harms and auditing

Adverse events will be collected, reported and assessed by the research team to determine severity and whether they are likely to be serious adverse events due to the trial. Serious adverse events and reactions will be reported to the relevant ethics committees and appropriate action taken, if any. Auditing will be carried out by the sponsor, Sheffield Hallam University. In the event of harm to participants arising as a result of the management, design or conduct of the research, Sheffield Hallam University insurance and indemnity policies will apply.

### Supervised exercise programme

Participants assigned to the exercise group will be invited to undertake two sessions of supervised exercise training each week for 8 consecutive weeks and three sessions of supervised exercise training each week for the final 4 consecutive weeks at CSES at Sheffield Hallam University. Each session will last approximately 60 min and will involve 40 min of an individualised exercise protocol performed either on a cycle ergometer or a motorized treadmill preceded by a 10 min warm-up and followed by a 10 min cool down.

The duration and intensity of the programme was selected based on evidence from exercise trials in PCOS that have identified that supervised, moderate-intensity exercise sessions between 50 and 70% VO_2max_ for a minimum of 12 weeks showed improvement in cardiometabolic risk factors such as TG, inflammation, and insulin resistance [3, 4, 15, 16].

Most of these studies involved three sessions per week [3, 15, 16]. However, to maximise adherence and reduce inconvenience to participants, the current trial comprises two sessions per week, at a duration of 1 h, increasing to three sessions per week for the final 4 weeks. Various research studies have shown that two sessions per week for 8 weeks can elicit improvements in microvascular endothelial function and exercise tolerance, both of which can reduce cardiovascular disease risk [17, 18], which is regarded as a key outcome in the current study. Additionally, the American College of Sports Medicine (ACSM) recommends a weekly duration of 60–150 min of exercise duration for inactive individuals or individuals who do not participate in any habitual physical activity [19].

ACSM’s Frequency, Intensity, Time and Type (FITT) principle recommends increasing one variable of the principle after at least one month of exercise. Extremely deconditioned to moderately deconditioned individuals are recommend to work at a moderate intensity of ~ 57–74% HR_max_, which correlates with previous exercise interventions in PCOS where workload is set to a VO_2max_ of 50–70% [19]. The programme therefore increases in intensity at increments of 4 weeks up to 74% HR_max_, allowing for progression while remaining moderate in effort and within the recommendations for moderately deconditioned individuals.

In order to calculate individual heart rate zones for each participant, a formula (206.9 − (0.67 × age)) will be used to calculate maximum heart rate [19]. Participants will wear a Polar T31 heart rate monitor chest strap and wristwatch for the duration of each session in order to monitor their heart rate and stay in the assigned zones.

### Lifestyle physical activity group

Participants randomized to the lifestyle physical activity group will attend CSES at Sheffield Hallam University for all the tests and measurements but will not take part in the structured exercise intervention. However, advice and information on how to increase physical activity will be provided using British Heart Foundation guidelines: ‘Get active, stay active’. This will be discussed during the informed consent consultation. Participants will be asked to monitor and track their daily physical activity using a smartphone fitness application. This will either be Google Fit or Apple Health, since these are the default fitness apps for Android and Apple phones and are often pre-installed. The research team will gain permission to access their recorded activity. Between the baseline measurements and those after 12 weeks, participants will receive regular telephone support, approximately once a week, to obtain information about their progress and provide advice as needed.

Participants in the control group will not undertake any intervention but will still receive standard care from their medical professional which may include general weight-loss advice. To improve adherence for the control group, the research team will offer all participants allocated to the group the opportunity to undertake supervised exercise sessions at the CSES after their successful completion of the trial.

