### Recruitment of participants

Participants will initially be screened according to inclusion criteria by a clinical member of the research team via a computerised search of their notes. Afterwards potential participants will be sent information packs about the research, including an invitation letter and participant information brochure. Email and contact information for the researcher will be included in the packs and potential participants will be given a minimum of 24 h and a maximum of 14 days to respond. It will be clearly stated in the invitation letter that there is no obligation or pressure to participate in the study and that if patients do not wish to participate, their future medical care will not be jeopardised.

Volunteers wishing to participate in the study will be requested to contact a member of the research team or respond via letter by a specified date. Participants who respond to the letter of invitation and satisfy triage through telephone pre-screening will be invited into CSES of the Sheffield Hallam University for their initial session, where they will provide written informed consent and have an opportunity to familiarise themselves with the protocol and ask questions. They will then undertake baseline assessments.

It will be assumed that those who haven’t contacted the research team could still potentially have an interest in study participation but may be too busy to respond. They will be re-contacted via telephone (or sent a follow-up letter if telephone contact cannot be established) to remind them of the invitation to the study. Potential participants who decline to volunteer or who do not respond to the follow-up letter will not be contacted further, since it will be assumed that they do not wish to participate in the study.

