### Baseline and post-intervention measurements

During visit 1, after written informed consent has been obtained and eligibility confirmed by AW, the following baseline tests measurements will be made: age, anthropometric measures (stature, body mass, hip and waist measurements), finger-prick and venous blood sampling (see Outcome measures for a detailed description of analytes), aerobic fitness assessed by the Astrand-Rhyming single stage test (see Outcome measures for detailed description).

After completion of the intervention, all tests and measurements will be repeated.

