### Randomisation and masking

Participants will be randomised in equal numbers between a supervised exercise programme, a lifestyle physical activity group and a control group. This will be undertaken using a computerised randomisation programme (QuickCalcs, GraphPad Software, USA) by an experienced researcher who is not involved in the study assessments. Allocation will be placed in sequentially labelled opaque envelopes. Each envelope will be offered to the participants, in sequence, by the chief investigator, on completion of their baseline assessments. It is not possible to mask participants or research team to the allocated intervention. Outcome assessors will be blinded to group allocation for anthropometric and fitness measures, but blood assays will be carried out by the same member of the research team. This is because blood assays are not considered to be subjective and are unlikely to be affected by outcome assessor bias.

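### The lifestyle arm's activity advice is placed at the consent consultation, before baseline and allocation, which conflicts with the protocol's own order of events

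*Protocol article*

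**What the plan says.** Under Lifestyle physical activity group, the protocol article sets out what women randomised to that arm receive. It says that "advice and information on how to increase physical activity will be provided using British Heart Foundation guidelines", and continues directly: "This will be discussed during the informed consent consultation". The same section adds tracking of daily activity with a smartphone application and telephone support about once a week. It also states that the control group has no study intervention, only standard care.

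Three other sections fix the order of events:

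- Recruitment of participants: women come to an initial session "where they will provide written informed consent and have an opportunity to familiarise themselves with the protocol and ask questions". The next sentence is "They will then undertake baseline assessments".
- Baseline and post-intervention measurements: the visit 1 tests are made "after written informed consent has been obtained and eligibility confirmed".
- Randomisation and masking: "Each envelope will be offered to the participants, in sequence, by the chief investigator, on completion of their baseline assessments". The envelopes are opaque and sequentially labelled.

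**The concern.** The advice is described only as part of the lifestyle arm, yet it is timed at a point every participant passes through before anyone has been allocated. Staff who followed the sentence would give future controls and future exercise participants a piece of the lifestyle intervention.

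Two things are at stake.

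- **The lifestyle-versus-control contrast.** If controls act on the advice, the difference between these arms shrinks. The Discussion says the study is meant to supply effect sizes for planning a full-scale trial, so the planning information would be affected. Control-arm activity and retention would also no longer describe women who had received nothing from the study.
- **The baseline activity measure.** Under Secondary outcomes, the long-form International Physical Activity Questionnaire (IPAQ) is given to all participants at baseline and after the intervention, to compare sitting time and lifestyle activity. Answers given shortly after advice to be more active may differ from answers given without it.

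Exposure of this kind cannot be undone once a woman has been enrolled.

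**Working it through.** No calculation bears on this point; the check is of sequence. The inputs are the four sections cited above.

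1. **Consent against baseline.** Recruitment of participants and Baseline and post-intervention measurements agree: consent comes first, and baseline follows.
2. **Baseline against allocation.** Randomisation and masking discloses the arm "in sequence, by the chief investigator, on completion of their baseline assessments". Baseline comes first, and allocation follows.
3. **Combined order.** Consent consultation, then baseline assessments, then envelope, then the 12-week intervention period.
4. **Where the advice falls.** Lifestyle physical activity group puts its discussion in the consent consultation. That is the first step, and allocation is the third.
5. **Who would hear it.** Since no arm is known at the first step, the advice cannot be confined to one arm. Data analysis gives 51 women, 17 per group. The women in the other two arms number 51 − 17 = 34: 17 exercise and 17 control.
6. **Is there a later point for the initial advice?** None is given. The only later contact described for this arm, before the post-intervention tests, is the telephone support, which covers progress and further advice where needed. The sentence cannot therefore be read as a preview of a delivery described elsewhere in the article.
7. **Does the baseline IPAQ fall after consent?** The article gives no exact position for it within the visit. It is a baseline study measurement, though, and baseline follows consent, so on the stated order it comes after the consultation.

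The statement about timing and the stated order of events therefore cannot both hold if the advice belongs to the lifestyle arm alone.

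**The case against.** The strongest reply is that the sentence is loose wording and not a plan to treat everyone. The advice is to be provided to women randomised to the arm, whereas what happens at consent is discussion. A consent consultation has to explain what each arm involves, and this one includes time for questions about the protocol. On that reading, everyone hears what the lifestyle arm entails and only allocated women receive the advice. This reading is possible, but the article does not state it and gives no other time for the initial advice. Fig. 1, the participant schedule, was not available for this check and might settle the timing. It would still leave the sentence needing correction.

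Several further points limit the consequences, and they stand:

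- The advice is one of three components. Controls would get neither the app tracking nor the calls, and withdrawal from the lifestyle arm is defined by stopping the app monitoring.
- Controls are not free of advice in any case, because standard care may include general weight-loss advice.
- Consent and baseline belong to the same initial visit, so advice given then could hardly change that day's blood, fitness or anthropometric results. At most it could colour self-reported activity, and it would do so irrespective of arm.
- The sample-size input the study chiefly seeks is the standard deviation of oxidised LDL, not the lifestyle-versus-control difference.

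A reader might also infer that allocation is known at consent, so that concealment is defeated. The documents do not support this: the randomisation section is explicit that envelopes are opaque and offered after baseline, and nothing suggests earlier disclosure.

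**Conclusion.** The text is wrong as written: the stated time of the lifestyle advice contradicts the stated order of consent, baseline and allocation. Severity is moderate. Recruitment, attendance and completion can be measured either way, the between-group comparisons are exploratory, and the article already cautions that all analyses may be underpowered.

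On the literal reading, 34 women outside the lifestyle arm would be exposed to one of its components. The likely direction is dilution of the lifestyle-versus-control contrast. That assumes the advice has some effect on its own and that controls act on it.

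A reader might want to turn this into a sample-size inflation for the full trial. That would need the share of the lifestyle effect carried by the advice alone. The documents give no such figure, and it could be near zero, so no multiplier is justified.

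**What to change.** Replace the sentence on the consent consultation in Lifestyle physical activity group, so that it agrees with Recruitment of participants, Baseline and post-intervention measurements, and Randomisation and masking. The new text should say two things:

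- the consent consultation gives only a neutral description of the three arms;
- the activity advice and information are given and discussed after the allocation envelope has been opened, and only with women allocated to the lifestyle group.

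If Fig. 1 shows the timing of the advice, check that it agrees.

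The cost is one sentence, plus a short conversation after allocation with the 17 lifestyle-group women. Sample size, measurements and analysis do not change.

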### Participant timeline

The Standard Protocol Items: Recommendations for Interventional Trials (SPIRIT) (Additional file 1) diagram shown in Fig. 1 outlines the participant schedule of enrolment, intervention, close-out and assessment time-points.

**Fig. 1 Fig1:**
[figure not shown]
Participant schedule of enrolment, interventions and assessments

### Outcome measures

#### Feasibility outcomes

The primary outcomes for this study are acceptability and feasibility of procedures for recruitment, allocation, measurement, and retention for the intervention procedures. Recruitment rate will be calculated by dividing the number of women eligible and consenting by the recruitment period. Attrition rates will be established as discontinuation of the intervention and loss to follow-up measurement for both conditions. Compliance will be monitored by session attendance and monitoring the data from recorded daily physical activity, with examination of reasons for drop-out or non-compliance. Reasons for drop-out will also be used to assess the suitability of allocation procedures. Suitability of measurement procedures will be evaluated by completion rates and reasons for missing data. The post-intervention interview will be used to assess the acceptability of the exercise programme and lifestyle physical activity group intervention, along with attendance and compliance data.

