### Withdrawals

Participants may withdraw at any time without providing a reason. They may also choose to withdraw their data from the study. A participant will be considered to be withdrawn if they request to leave the trial or they are lost to follow-up. If allocated to the exercise group, participants will be considered as withdrawn if they no longer attend the supervised exercise sessions, and in the lifestyle physical activity group if they no longer monitor daily physical activity through the fitness application. Data from withdrawn participants will not be used; only data from participants who completed the intervention and baseline and post-intervention assessments will be used in analysis.

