### Data analysis

All quantitative measurements will be presented as mean ± standard deviation (SD) unless otherwise stated.

As this is a feasibility study, no formal sample size calculation was required. The sample size for a feasibility study needs to strike a balance where it does not cause undue burden on participants by being too large, but not be too small that critical parameters (such as consent rate, attrition, and compliance) cannot be precisely estimated and used for the calculation of a full-scale RCT. It has been posited that a rule of thumb of at least 30 participants overall should be sufficient for a feasibility trial [23].

Additionally, sample sizes between 24 and 50 have been recommended to calculate a standard deviation of an outcome that can then be entered into a formal power calculation for the full-scale RCT [24, 25]. Oxidised LDL concentrations are a secondary outcome for the proposed study, and a sample size within this remit will provide a reliable standard deviation for oxidised LDL to be used in a power calculation. Since there are three groups, a total sample size of 51 will allow even numbers across three groups (17 in each group).

Descriptive statistics will be used to characterise the groups at baseline and post-intervention. Pre and post-intervention means will be recorded for each group. Difference between means will be assessed using two-factor mixed-ANOVAs where the effect of two independent variables (grouping and time point) will be measured on the dependent variables. The within-subjects factor is time, and the between-subjects factor is group. Post-hoc analysis will be undertaken in the event of any significant differences in group means. Data will be assessed to ensure the assumptions of the mixed-ANOVA are met including checks for normality.

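### The attrition definition covers two conditions in a three-arm trial and joins stopping the intervention with losing the outcome, so it does not reliably give the full RCT's drop-out allowance

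*Protocol article*

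**What the plan says.** The section on feasibility outcomes gives the primary outcome: "The primary outcomes for this study are acceptability and feasibility of procedures for recruitment, allocation, measurement, and retention for the intervention procedures". It then defines attrition: "Attrition rates will be established as discontinuation of the intervention and loss to follow-up measurement for both conditions".

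The design has three arms: "Participants will be randomised in equal numbers between a supervised exercise programme, a lifestyle physical activity group and a control group". The size is fixed accordingly, as "a total sample size of 51 will allow even numbers across three groups (17 in each group". The control group has no intervention; it receives standard care only (Lifestyle physical activity group, last paragraph).

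The Withdrawals section ties stopping the intervention to withdrawal. For the exercise arm: "If allocated to the exercise group, participants will be considered as withdrawn if they no longer attend the supervised exercise sessions". For the lifestyle arm, the same holds "in the lifestyle physical activity group if they no longer monitor daily physical activity through the fitness application". Their results then drop out: "Data from withdrawn participants will not be used; only data from participants who completed the intervention and baseline and post-intervention assessments will be used in" the analysis.

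The Data analysis section explains what attrition is for. The sample must not be so small that "critical parameters (such as consent rate, attrition, and compliance) cannot be precisely estimated and used for the calculation of a full-scale RCT".

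**The concern.** Two things are wrong with the definition.

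First, *both conditions* has no clear referent in a trial with three groups. It may mean the two active arms, or it may be wording left from a two-arm text. Either way, a primary outcome definition disagrees with the design.

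Second, the sentence names two events that answer different questions. Stopping sessions or app logging concerns adherence and acceptability. Missing the post-intervention measurement concerns loss of data. A sample size for an RCT is normally inflated for missing outcomes, and a woman who stops logging but still gives a week-12 blood sample has not lost hers. The first event cannot occur in the control arm, so a joint rate would not be comparable across arms. In the lifestyle arm it could largely reflect app use.

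At stake is a figure that the feasibility trial exists to supply: how many extra women the full RCT must randomise, and whether loss differs between groups.

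**Working it through.** **The plan's own figure.** 3 arms × 17 = 51, which agrees with the Data analysis section. The article states no expected attrition rate and no drop-out allowance, so there is no further figure to reproduce. The counts below are assumptions that show direction and rough size.

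**Formula.** For a future RCT needing 100 evaluable participants and a loss proportion d, the number to randomise is N = 100 / (1 − d), rounded up.

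**Step 1: joining the two events.** Let L women of 51 have no post-intervention outcome, and let S more stop the intervention but could be measured. The joint rate is (L + S)/51; outcome loss is L/51.

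| L | S | Joint rate | N | Outcome loss | N |
|---|---|---|---|---|---|
| 2 | 0 | 2/51 = 3.9% | 105 | 2/51 = 3.9% | 105 |
| 2 | 4 | 6/51 = 11.8% | 114 | 2/51 = 3.9% | 105 |
| 5 | 5 | 10/51 = 19.6% | 125 | 5/51 = 9.8% | 111 |
| 5 | 10 | 15/51 = 29.4% | 142 | 5/51 = 9.8% | 111 |

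For example, 100 / (1 − 10/51) = 124.4, so 125, and 100 / (1 − 5/51) = 110.9, so 111. With S = 0 the two rates are equal and nothing is overstated.

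**Step 2: which arms are counted.** Suppose 5 of 17 are lost in each active arm. Read as the two active arms, the rate is 10/34 = 29.4%, giving N = 142. Over all three arms it depends on the control losses:

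| Control losses | Rate over 51 | N |
|---|---|---|
| 0 | 10/51 = 19.6% | 125 |
| 1 | 11/51 = 21.6% | 128 |
| 5 | 15/51 = 29.4% | 142 |
| 8 | 18/51 = 35.3% | 155 |

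Leaving controls out can therefore push the allowance either way.

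**Step 3: precision.** Exact 95% intervals are wide: 5/17 gives 10.3% to 56.0%; 5/51 gives 3.3% to 21.4%; 10/51 gives 9.8% to 33.1%.

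**Step 4: can outcome loss be recovered from elsewhere in the article?** The feasibility section also promises measurement completion rates, with reasons for missing data and for drop-out. These bear on outcome loss, but they are offered as a check on the measurement procedures and are not stated by arm. They help only if women who stop are still invited back. The section on baseline and post-intervention measurements places the repeat tests after completion of the intervention, and the Withdrawals section treats those who stop as withdrawn. Neither secures that visit.

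**The case against.** The strongest reply is that the sentence speaks of rates in the plural and names two components, so it can be read as two separate rates, which is what this point asks for. The completion rates and reasons for missing data supply a second route to outcome loss. The aims in the Background include measuring retention with no arm excluded. The general withdrawal rule (asking to leave, or loss to follow-up) covers controls, for whom loss to follow-up measurement is perfectly well defined. Under the completers-only rule in the Withdrawals section, a woman who stops really is not evaluable, so a joint rate would be the matching allowance if the full RCT kept that rule. Finally, denominators and intervals are details that an article may leave to the full protocol.

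Much of this stands. The article does not say that a single composite will be reported, and missing detail on intervals is not the complaint. What remains is that a stated definition disagrees with the number of arms and does not say that its two events are kept apart, while the Withdrawals section treats stopping as withdrawal in the active arms only. No plan to keep the completers-only rule in the full RCT is stated.

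A reader might go further and infer that control attrition will not be reported, or that controls are expected to leave out of disappointment. The first is only one reading of *both conditions*. The second is not in the article, which says only that later exercise sessions are offered to improve adherence in that group.

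**Conclusion.** The point holds as a flaw in a stated primary outcome definition. As worded, attrition does not fit a three-arm trial, leaves the control rate unclear, and may overstate outcome loss in the active arms. It therefore does not reliably give the RCT's drop-out allowance. To say that it cannot give the allowance at all would go too far, because completion data are also promised.

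The size is illustrative only: 125 to 142 randomised per 100 evaluable instead of 111, assuming 5 of 51 with no outcome and 5 to 10 more who stop but could be measured. It falls to zero if everyone who stops also misses the assessment. A starker one-arm example is easy to build: if 5 of 17 lifestyle participants stop logging but all are measured, the inflation factor is 1/(1 − 5/17) = 1.42 against 1.00. That is an assumed extreme. With no other losses, the same five women are 5/51 = 9.8% of the trial, a factor of 1.11, so 42% should not be taken as the expected error.

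**What to change.** Replace *both conditions* with *all three groups*, and state two rates, reported separately by arm with all randomised women as the denominator and 95% confidence intervals:

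1. No post-intervention oxidised LDL measurement, whatever the adherence, in all three groups. Use this for the RCT's drop-out allowance.
2. Discontinuation of the allocated intervention, in the exercise and lifestyle groups only.

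Reconcile this with the sections on withdrawals and on baseline and post-intervention measurements, so that a woman who stops the intervention but attends the post-intervention assessment is not counted as outcome loss.

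The change of wording is short. The practical cost is that women who stop must still be invited to the post-intervention visit. With 17 per arm the by-arm rates will be imprecise, and the report should say so.
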